## Abstract

**Background:**

Community-based interventions have shown promise in addressing the childhood obesity epidemic. Such efforts rely on the knowledge of key community members and their engagement with the drivers of obesity in their community. This paper presents the protocol for the measurement and evaluation of knowledge and engagement among community leaders within a whole-of-community systems intervention across 10 large intervention communities in Australia.

**Methods:**

We will investigate the role of stakeholder knowledge and engagement in the implementation and effectiveness of the stepped wedge cluster randomised trial in ten communities in Victoria, Australia. Data will be collected using the Stakeholder-driven Community Diffusion Survey (SDCD) to measure levels of knowledge and engagement prior to commencement (2019), across the three separate levels of governance within the intervention at five time points. Primary outcomes will be baseline overall knowledge and engagement scores across the three levels of governance and change in overall knowledge and engagement over time.

**Discussion:**

We hypothesise there will be heterogeneity between intervention sites on levels of knowledge and engagement and that these differences will be associated with variability in implementation success.

**Trial registration:**

Australian New Zealand Clinical Trials Registry ACTRN12618001986268. Registered on 11 December 2018

## Introduction

### Background

Addressing childhood obesity is an international priority [1]. Within Australia, almost 25% of Australian children aged 5–17 experienced overweight or obesity in 2017–2018 [2]. There is evidence that the actual prevalence may be far higher than national surveys with relatively low response rates [3]. It is clear that childhood obesity significantly impacts quality of life and mental health [4]. As childhood obesity tracks into adulthood [5], leading to ever more serious health consequences, there is an urgent need to intervene early if the health and social and economic impacts of obesity are to be addressed [6].

A major challenge to the prevention of childhood obesity is the complexity arising from its multiple interdependent and systemic causes, ranging from individual biology through to environmental drivers of food and physical activity choices [1]. The importance of a systems approach to addressing childhood obesity is supported by the existing trial evidence that suggests multi-component and multi-level interventions that increase community capacity and include both healthy eating and physical activity are more likely to have a positive impact [7]. Several systematic reviews have highlighted that the prevention of childhood obesity is possible through comprehensive community-based interventions [8–10] and engaged leadership and relevant support structures and capacity [11]. Noteworthy interventions have included Shape Up Somerville in the USA [12]; Be Active Eat Well [13], It’s Your Move [14] and Romp & Chomp [15] in Australia; Fleurbaix and Laventie in Northern France [16]; and Children’s Healthy Living [17] in the Pacific region.

Consistent with the need to address complexity, Swinburn et al. [18] pointed to a third generation of community-based intervention trials that explore what works within different system contexts and how existing systems can be strengthened to prevent disease. There are now several major examples internationally of large scale interventions meeting this challenge, intervening across multiple communities and taking an explicitly complex systems approach to engaging communities and catalysing action [19–22]. Such approaches have potential to optimise implementation approaches because they emphasise “…capacity building, creativity and innovation, relationships, engagement, communication, embedded action and policies, robustness and sustainability, facilitative leadership, and embedded monitoring and evaluation” [23] p. 2.

Intervening at a different level necessitates different tools to evaluate the effectiveness of these actions. The tools required to measure these elements have evolved over time. Community capacity measures focus primarily on the four domains of leadership, resources, partnership and intelligence [24], and community readiness, measures that explore the five domains of knowledge of the issue, awareness of efforts to address the issue, community climate, leadership and resources [25]. The common elements within these tools emphasise the importance of knowledge, resources and leadership. These constructs, although shown to relate to successful obesity prevention [26], are difficult constructs to measure [27] and were not specifically designed to measure changes in underlying determinants of obesity over time.

Korn et al. [28] developed a tool that includes the major concepts we aim to measure in systems change: knowledge, resources and leadership, and extended the relevance to systems change by looking at the specific characteristics that leaders require to catalyse change and diffuse innovation effectively throughout the community with a specific focus on the prevention of childhood obesity. The resulting Stakeholder-driven Community Diffusion (SDCD) Survey assesses several domains which quantifies the knowledge about the problem of obesity, knowledge about effective and sustainable interventions, available resources, mutual learnings, flexibility, leadership and trust (defined as belief and confidence in others). This tool aligns with previous attempts to measure concepts of readiness and capacity but refines these through an emphasis on understanding the drivers of success in community-based system-level interventions and a focus on core elements identified in the literature that diffuse innovation and catalyse change through communities.

#### Problem statement

Despite increasingly complex intervention approaches, there has been little progress in understanding how community leaders’ knowledge, engagement and social networks contribute to the success or otherwise of community-based interventions. This is partly due to a historical focus on evaluating outcomes from single community trials, with less emphasis on the specific characteristics that may lead to successful outcomes within these trials and across broader multi-community trials.

This paper presents the protocol for the measurement and evaluation of knowledge and engagement among community leaders’ for the Reflexive Evidence and Systems interventions to Prevent Obesity and Non-communicable Disease (RESPOND) trial, a whole-of-community systems intervention across 10 large intervention communities (local government areas (LGAs)) in Victoria, Australia. This protocol follows the SPIRIT checklist for guidance in the reporting of protocols for clinical trials [29]. The measurement of leaders’ knowledge and engagement over multiple time points, along with intervention process measures, will enable investigation of the following research questions:
RQ1: What is the baseline level of community leaders’ knowledge and engagement in each of the governance and implementation groups within the project and how does it differ between communities?RQ2: How do levels of knowledge and engagement among community leaders change during participation in a whole-of-community systems intervention?RQ3: To explore whether knowledge and engagement levels, and/or changes in knowledge and engagement levels, predict implementation effectiveness of system-level intervention?

Our hypothesis is that there will be heterogeneity between intervention sites on baseline levels of knowledge and engagement and that these differences will be associated with variability in implementation success and level of intervention within a system. The level of system intervention actions will be evaluated against the Meadows framework [30]. This assessment includes, for example, changes to a variable, connections between these variables, rules governing the system and goals of the system [30].

## Methods

RESPOND utilises systems approaches in the design, implementation and evaluation of a large-scale intervention to prevent obesity among children aged 0–12 years. It has prospective registration as a clinical trial [31], and is a stepped-wedge cluster randomised trial in 10 communities. This protocol explains one sub-study of the RESPOND trial that relates to changes in knowledge and engagement.

The setting for the trial is the Ovens Murray and Goulburn regions of north eastern Victoria, Australia Fig. 1, which covers a population of approximately 30,000 children (aged 0–12 years) [32]. For the purpose of trial design, communities are defined as local government areas (LGAs), which are the geographical divisions administered by municipal governments within Australian states and the Northern Territory [33]. The unit of randomisation and intervention (clusters) is the LGA (rather than individual children or townships). The ten LGAs will be ranked in order of population size and divided in five pairs. A computer-generated random list will be generated by the study statistician who will not be involved with any aspect of the enrolment process and has no contact with the communities. One community from each pair will be randomly allocated to receive the intervention at step 1. Blinding is not feasible in this trial as the whole community is recruited into the design, implementation and evaluation.

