### Data management and analysis plan

The responses to each SDCD survey question will be coded from 0 (strongly disagree) to 1 (strongly agree) [0 = 0 strongly disagree, 0.25 = disagree, 0.50 = agree, 0.75 = agree, 1.00 = strongly agree]. Domain summaries are the average of items within each domain. Participant summaries are averages of the domains (domain-weighted rather than item-weighted). We view the domains as equally important as each other, and the number of items is not related to how important the domains are, rather the complexity of eliciting the information about each domain. The SDCD survey will be summarised at participant level as the average of items within each of the five domains of knowledge (5 knowledge sub-scores) and the five domains of engagement (5 engagement sub-scores) (see Table 3).
*Analysis*: RQ1: What is the baseline level of community leaders’ knowledge and engagement in each of the governance and implementation groups within the project and how does it differ between communities?

Variability of scores and sub-scores of knowledge and engagement at baseline across participant communities will be estimated based on surveys completed by participants in the Local Implementation Groups. Of note, ‘baseline’ corresponds to the 2019 survey for step 1 communities and to the 2021 survey for step 2 communities. Variability across communities will be estimated using a linear mixed model (multi-level) with community as the random factor.
*Analysis*: RQ2: How do levels of knowledge and engagement among community leaders change during participation in a whole-of-community systems intervention?

We will fit linear mixed models with time as fixed effect and participant as random effect (to account for the repeated measurements) to assess whether a temporal trend exists in the SDCD scores (and sub-scores) and whether the intervention induces changes in trends of SDCD scores. For Regional Implementation Network participants/communities, the model will further include community allocation to step 1 or 2 as fixed effect, and the breakpoint (2021) to allow for changes in slope in step 2 communities. For Local Implementation Groups, the model will additionally include community as a random effect to account for clustering. If for any participant group a linear relation between a given score and time is not supported by the data, time will be incorporated as a categorical variable.

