*Analysis*: RQ3: Explore whether average community baseline knowledge and engagement levels and/or average community changes in knowledge and engagement levels are associated with implementation effectiveness of system-level intervention.

For each community, data on knowledge and engagement of community leaders at baseline and changes in knowledge and engagement will be summarised using location and dispersion measures. We will explore whether these measures are associated with implementation effectiveness (number of actions implemented by the community) using nonparametric correlation and if appropriate linear models.

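### RQ3 correlates leaders' scores with a raw count of actions across ten communities of unequal size and implementation time; population size, the pairing factor, enters no stated analysis

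*Protocol article*

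**What the plan says.** The Methods section of the protocol article describes matched-pair randomisation of local government areas: "The ten LGAs will be ranked in order of population size and divided in five pairs", and then "One community from each pair will be randomly allocated to receive the intervention at step 1".

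Under Data management and analysis plan, the model terms are named by research question:

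- **RQ1:** a mixed model with community as the only random factor.
- **RQ2:** time as a fixed effect and participant as a random effect. For the Regional Implementation Network, "the model will further include community allocation to step 1 or 2 as fixed effect", together with a 2021 breakpoint. For the Local Implementation Groups, "the model will additionally include community as a random effect to account for clustering".
- **RQ3:** community-level summaries of scores, at baseline and as change, are related to "implementation effectiveness (number of actions implemented by the community") by nonparametric correlation and, where suitable, linear models.

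No size or pair term appears in RQ1, RQ2 or RQ3, and the RQ3 count has no denominator. Under Outcomes, community groups are surveyed from the time they come into existence: 2019 for step 1 and 2021 for step 2.

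**The concern.** RQ3 compares two observed characteristics of ten communities. Random allocation to step does nothing to make communities with high and low scores alike in other respects. The design itself ranks these communities by size. A larger community may run more actions whatever its leaders know, and its leaders may also score differently, for example on the resources items of the survey. If both hold, size alone produces an association between scores and actions. With opposite signs it could hide one.

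The raw count also mixes unequal exposure. If actions are counted to 2023, step 1 communities have had about four years (2019 to 2023) and step 2 communities about two (2021 to 2023). Change since baseline is measured over the same unequal spans.

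RQ3 is exploratory, but it addresses the article's stated hypothesis that differences in knowledge and engagement go with differences in implementation success. A result driven by size or duration could be read as support for that hypothesis.

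**Working it through.** **The plan's own figures.** The article gives no power, variance or correlation figure on this point. Its one sample figure, a maximum of 4270 observations, reproduces from Table 1 and the survey rounds: 44×5 + 10×5 + 5×100×5 + 5×100×3 = 220 + 50 + 2500 + 1500 = 4270. RQ3, however, is analysed on 10 communities.

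**RQ3, effect of size.** *Assumptions:* two-sided 5% test; no direct link between scores and actions; size correlates a with actions and k with scores. The induced correlation on the underlying scale is a×k. *Check:* 40,000 simulated data sets of 10 communities for each pair of values. The unadjusted test was Spearman's, with critical value 0.648. The adjusted test was the rank correlation partialled for size, with 7 df.

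| a / k | a×k | Mean Spearman | False positives, raw | False positives, partialled |
|---|---|---|---|---|
| 0 / 0 | 0 | 0.00 | 4.7% | 5.2% |
| 0.3 / 0.3 | 0.09 | 0.08 | 5.4% | 5.3% |
| 0.5 / 0.5 | 0.25 | 0.22 | 9.4% | 5.5% |
| 0.7 / 0.5 | 0.35 | 0.31 | 14.2% | 5.7% |
| 0.7 / 0.7 | 0.49 | 0.43 | 25.5% | 5.9% |

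If either correlation is zero, the raw test stays at about 5%. The effect of unequal implementation time was not simulated and would be separate.

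**Cost of partialling.** The critical correlation is t/√(df + t²):

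- 8 df: 2.306/√(8 + 5.318) = 0.632
- 7 df: 2.365/√(7 + 5.591) = 0.666

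**Dividing by population instead.** Suppose action counts do not scale with population, and log count and log population are independent with equal SDs. Then log rate = log count − log population, and its correlation with log population is −1/√2 = −0.71. If scores correlate 0.5 with size, the induced correlation is −0.71×0.5 = −0.35. That matches in magnitude the 0.7 / 0.5 row above, where about 14% of tests are falsely positive.

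**RQ2, contrast in level between steps (5 v 5 communities).** Let s be the share of between-community variance explained, and take that variance as the whole error. The interval width relative to no adjustment is (t_adj/2.306)×√(1−s).

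- One size covariate (7 df, t = 2.365): 1.02 at s = 0, 0.92 at 0.2, 0.73 at 0.5. Break-even at 1 − (2.306/2.365)² ≈ 0.05.
- Fixed pair terms (4 df, t = 2.776): 1.20 at s = 0, 1.08 at 0.2, 0.85 at 0.5. Break-even at 1 − (2.306/2.776)² ≈ 0.31.
- Ignoring the pairing makes the test conservative, not biased: simulated type I error is 5.0% at s = 0 and 1.3% at s = 0.5.

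**The case against.** The strongest case against is that this is an omitted covariate, which an article may leave to an analysis plan that is not shown, and that RQ3 is an exploratory correlation in ten communities whose form is left partly open. That limits the weight of the point. It does not remove it, because the article names its RQ2 model terms and fixes the RQ3 outcome as an unscaled count.

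A reader might infer that size is a known confounder. The documents do not support this. Size is used only to form pairs, in a parent trial whose primary outcome is children's BMIz, and nothing says that it drives scores or actions. The RQ3 figures rest wholly on assumed correlations.

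A reader might also infer that leaving the pairing factor out biases the step comparison or clearly costs precision in RQ2. Neither follows. Pairing balances size across steps. The calculated gain concerns a contrast in level, whereas RQ2 asks about change and slope, on which a size term has little effect. The step term is explicit only for the Regional Implementation Network, which Table 1 puts at one person per community. At the anticipated 65% response that is 6 or 7 people, and variation between persons and occasions would dilute any gain. The RQ2 widths are therefore best cases.

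The objection to per-child scaling also stands: used alone, it can create the kind of association it is meant to remove.

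**Conclusion.** The point holds for RQ3 and is minor. The stated analysis correlates scores with a raw action count across communities that differ in size and implementation time, and adjusts for neither. If size relates to both variables at 0.5, the false-positive rate is about 9%; at 0.7 it is about 26%; at 0.3 the excess is negligible. The documents give no basis for choosing among these values, so the conclusion is that a size effect cannot be ruled out as planned, not that one exists. For RQ2 there is no bias, only a possible gain in precision for level contrasts. An analysis plan not shown may already deal with some of this.

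**What to change.** **RQ3:** Express actions per year of implementation, stating when each community's clock starts and when counting stops. Beside the raw-count correlation, report the rank correlation partialled for log population (if size is itself ranked, as in the check, the log makes no difference). The population ranking is already held from randomisation, so no new data are needed for size. The cost is one degree of freedom: the critical correlation rises from 0.63 to 0.67. With ten communities, adjustment for more than one covariate is not realistic. Do not rely on actions per 1,000 children alone.

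**RQ2:** State whether size enters the models that contain step. One log-population covariate is optional, for level contrasts only. Fixed pair terms are not advised with five pairs, because they leave 4 df and lose precision unless they explain more than about 31% of between-community variance.

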**Fig. 1 Fig1:**
[figure not shown]
Trial setting: Ovens Murray and Goulburn regions of north eastern Victoria, Australia

The primary outcome for RESPOND is a change in children’s standardised body mass index (BMIz) among primary school-aged children in Grade 2 (aged approx. 7–8 years), Grade 4 (aged approx. 9–10 years) and Grade 6 (aged approx. 11–12 years). Secondary outcome measures include modifiable obesogenic risk factors of children (physical inactivity, sedentary behaviour, poor diet quality, poor sleep and health-related quality of life) and wellbeing of children attending schools in participating communities, at each of three measurement waves (June 2019, 2021 and 2023).

### Participants

Members of each of the groups within the RESPOND governance structure (as shown in Fig. 2) will be invited to participate in the Knowledge & Engagement Survey. This includes a single overarching Regional Partners Group (RPG) which comprises senior executive representation from all partners to the National Health and Medical Research Council (NHMRC) grant. This to date includes in alphabetical order: Beechworth Health Service, Central Hume Primary Care Partnership, Gateway Health, Goulburn Valley Primary Care Partnership, Greater Shepparton City Council, Lower Hume Primary Care Partnership, Numurkah District Health, Upper Hume Primary Care Partnership, VicHealth, the Victorian Department of Education and Training, the Victorian Department of Health and Human Services and Yarrawonga Health. This group provides overarching direction and governance of the RESPOND project. The Regional Implementation Network (RIN) comprises operational and co-ordinator level staff from each of the partner agencies (listed above), along with representation from each of the implementation communities (who are not necessarily signed partners to the grant). This network provides connections and knowledge exchange between the RPG and the individual communities and provides a forum for learning and sharing of experience among the individual communities. The third group comprises the 10 community action groups (CAG), one within each community whose role is to coordinate the implementation of local intervention activities. Participants will be invited to participate in the trial at each data collection point. Any contact details obtained at baseline or at follow-up data collection points will be retained subject to our ethics approvals and used for follow-up data collection. We will send three reminders to request participants to participate in data collection.

**Fig. 2 Fig2:**
[figure not shown]
The RESPOND Governance Structure

The number of possible participants will be used as the denominator and is based on maximum possible participation across all tiers of the governance structure and implementation teams (Table 1).

**Table 1 Tab1:** Sampling frame: groups and estimated maximum respondent numbers per community

Governance groups	Members	Number of groups	Estimated* maximum possible participants per group	Estimated* maximum possible number of responses per time point	Proposed timelines
Regional Partners Group (RPG)	Signatories to the funded grant	1	44	44	Feb/Mar 2019–2023
Regional Implementation Network (RIN)	One prevention staff member from each community (*n* = 10)	1	10	10	Feb/Mar 2019–2023
Community Action Groups (CAG)	Participants of three workshops and community-led strategies	10	100	1000	Feb/Mar 2019–2023

*Estimated maximum participant numbers based on the current number of 12 partner organisations which may increase or decrease throughout the life course of the grant

Including baseline, for the Knowledge and Engagement Survey, there are five data collection points over the 5-year period of the grant in step 1 communities, and three data collection points in step 2 communities (this survey is administered annually). It is theoretically possible that a maximum of 4270 observations could be collected.

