### Outcomes

The SDCD will measure levels of knowledge and engagement prior to commencement, during intervention (annually, 2019–2023) and at the end of the intervention (2023). The Regional Partners Group and Implementation Network will be surveyed at all five time points, while the community-specific Community Action Groups will be surveyed annually from the time the groups come into existence post GMB 3 (2019 for step 1, 2021 for step 2).

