### Recruitment

The survey will be completed online, and all potential participants will receive an email link to the survey. The Regional Partner Group will be directly invited to participate by the researchers, through contact lists for the RESPOND project quarterly meetings, which are convened and chaired by the University-based operational team (Fig. 2). The project partner organisations are responsible for convening the RIN and CAG; therefore, through third party recruitment, these partner organisations will send the survey invitations to all participants at those levels so that the researchers and partner agencies do not break the Victorian Privacy and Data Protection Act 2014 [35]. Based on previous experience of our group in similar surveys, we anticipate a response rate of 65% for the RPG and RIN and a response rate of 40% for the CAG.

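### The stated denominator is a planning maximum rather than the number invited, and Table 1 and the Participants text disagree on who belongs to the Regional Implementation Network

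*Protocol article*

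**What the plan says.** All places are in the protocol article.

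- **Denominator.** The sentence that introduces Table 1 (Participants) reads: "The number of possible participants will be used as the denominator and is based on maximum possible participation across all tiers". The table's footnote describes the figures as "Estimated maximum participant numbers based on the current number of 12 partner organisations which may increase or decrease throughout the life course of the grant".
- **Who is invited.** Participants says that members of every governance group will be invited at each data collection point. For the network and the action groups, Recruitment says "these partner organisations will send the survey invitations to all participants at those levels". It anticipates response rates of 65% for the Regional Partners Group and the network, and 40% for the action groups.
- **Network membership.** Table 1 describes the network as "One prevention staff member from each community" and gives it 10 members. The text above the table says it "comprises operational and co-ordinator level staff from each of the partner agencies (listed above), along with representation from each of the implementation communities". That text lists 12 partners.
- **Action groups.** Table 1 gives 10 groups of 100, hence 1000 responses per time point, with the timeline 2019–2023. Outcomes says the groups are "surveyed annually from the time the groups come into existence post GMB 3 (2019 for step 1, 2021 for step 2". The paragraph under Table 1 gives step 1 communities five collection points and step 2 communities three, with a theoretical maximum of 4270 observations.
- **Use of network membership.** Under RQ2, the data management and analysis plan adds community allocation to step 1 or 2, and a 2021 breakpoint, to the model for the network.

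**The concern.** A response rate should divide the number who answered by the number who were asked. Here the base is a rounded ceiling set in advance, the same 100 for every action group whatever its real size. The achieved rate would then mix non-response with group size. It could not be compared with the anticipated 40%, nor fairly between communities. The Data monitoring section gives low response a practical role, since data from communities with low rates get an additional identifiability check. With a fixed base of 100, that check would respond to the number of respondents and not to the proportion who declined.

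The two descriptions of the network matter for a second reason. If the network is one person per community, every member has a step allocation. If it also includes staff of partner agencies, among them state government departments, the article gives no step allocation for those people. The RQ2 model for the network needs one.

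**Working it through.** **Inputs.** Table 1: partners group 44, network 10, action groups 10 × 100. Collection points: five for the partners group, the network and step 1 action groups; three for step 2 action groups (text under Table 1; Outcomes). Communities: five per step, because one of each of five pairs is allocated to step 1 (Methods). Anticipated rates: 65% and 40% (Recruitment).

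**1. The plan's own total.**
44×5 + 10×5 + (5×100)×5 + (5×100)×3 = 220 + 50 + 2500 + 1500 = 4270. This reproduces the stated figure exactly. It uses 500 action group members in 2019 and 2020, and 1000 from 2021. Reading the per-time-point column literally over five waves gives (44 + 10 + 1000)×5 = 5270, which does not match. The total therefore already reflects the staggered start, and the action group row of Table 1 is what fails to show it.

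**2. Action group rate on a base of 100.** The article does not give actual group sizes, so 30 to 70 invitees is an assumption. Reported rate = 0.40 × invitees / 100.

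| Invitees | Responders at 40% | Reported rate |
|---|---|---|
| 30 | 12 | 12% |
| 50 | 20 | 20% |
| 70 | 28 | 28% |
| 100 | 40 | 40% |

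The rate is right only if a group really has 100 invitees.

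**3. Network size and rate on a base of 10.** The text requires staff from each of 12 agencies plus community representation. With one person per agency, and every community representative also being one of those people, the size is 12. With one per agency, one per community and no overlap, it is 12 + 10 = 22. An intermediate case is 12 agencies plus the five step 1 communities, which is 17. Reported rate = 0.65 × members / 10. Total = 220 + 5 × members + 4000.

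| Members | Responders at 65% | Reported against 10 | Maximum total |
|---|---|---|---|
| 10 | 6.5 | 65% | 4270 |
| 12 | 7.8 | 78% | 4280 |
| 17 | 11.05 | 110% (110.5%) | 4305 |
| 22 | 14.3 | 143% | 4330 |

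At a true 65%, the reported rate passes 100% once membership exceeds 10/0.65 = 15.4. The total rises by 10 to 60, which is 0.2% to 1.4% of 4270.

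**The case against.** The case for leaving the text alone has several parts.

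- **The sentence does not name the response rate.** This is true, so the link is an inference. It is the natural one: the article gives anticipated response rates and shows no other use for a denominator.
- **Possible participants and invitees may coincide, and the footnote allows the estimates to move.** This would answer the point if the base were updated to the real membership. But the sentence ties the base to maximum possible participation, and the footnote ties movement to the number of partner organisations, not to the size of each action group.
- **The network need not have 22 members.** This stands. Participants says the communities are not necessarily signed partners, which leaves room for some that are, and one listed partner is a city council. One person could fill both roles. The contradiction does not depend on 22, however, since 12 agencies alone exceed 10.
- **Response rates enter no outcome and no listed analysis.** This also stands, and it limits the importance of the denominator.

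A reader might go further in three ways that the documents do not support. One is that 4270 is a mistake; it reproduces exactly. Another is that the plan overlooks the step 2 start, so that 40% of 500 in 2019–2020 (200 responses) would be reported as 20% of 1000. The text under Table 1 and the Outcomes section both handle that start, and 1000 is correct for 2021–2023. Only the table row is loose. The third is that network rates above 100% are certain; at the planned 65% that needs 16 or more members.

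**Conclusion.** The concern holds in a limited form. As written, the denominator understates the response rate of any action group with fewer than 100 invitees: 12% to 28% in place of 40%, if groups have 30 to 70 invitees. Table 1 and the Participants text contradict each other on the network. If the text is right, a true 65% would be reported as 78% to 143%, and the maximum total would be 4280 to 4330. These ranges rest on the assumed group sizes, on one person per agency, and on full or no overlap between agency staff and community representatives.

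The contradiction itself needs no assumption about overlap, and it has one consequence for analysis: it decides who can carry a step allocation in the RQ2 network model. Nothing here biases the action group estimates. The plan should be changed on this point, but it does not threaten the study's main results.

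**What to change.** 1. Define the denominator as the number of people invited, per group and per wave. For the network and action groups, ask the partner organisations that send the invitations to return a count. A count contains no personal data, so it fits the privacy reason for third-party recruitment. Keep the Table 1 figures as planning estimates only.
2. Reconcile the network's membership between Table 1 and the Participants text, and restate 4270 if the number changes.
3. Split the action group row of Table 1: 500 per time point for 2019–2020 and 1000 for 2021–2023.
4. State how network members without a community step allocation are handled under RQ2. One option is to fit the step and 2021 breakpoint terms to community representatives only. This is an analysis choice and should be fixed in advance.

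The cost is one count request per partner per wave, a few table edits, and possibly fewer network members in the step model.
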